## Abstract

**Background:**

Ankle sprains continue to pose a significant burden to the individual athlete, as well as to society as a whole. However, despite ankle sprains being the single most common sports injury and despite an active approach by various Dutch organisations in implementing preventive measures, large-scale community uptake of these preventive measures, and thus actual prevention of ankle sprains, is lagging well behind. In an attempt to bridge this implementation gap, the Dutch Consumer Safety Institute VeiligheidNL developed a freely available interactive App (‘Strenghten your ankle’ translated in Dutch as: ‘**Versterk je enkel**; available for iOS and Android) that contains - next to general advice on bracing and taping - a proven cost-effective neuromuscular program. The ‘Strengthen your ankle’ App has not been evaluated against the ‘regular’ prevention approach in which the neuromuscular program is advocated through written material. The aim of the current project is to evaluate the implementation value of the ‘Strengthen your ankle’ App as compared to the usual practice of providing injured athletes with written materials. In addition, as a secondary outcome measure, the cost-effectiveness will be assessed against usual practice.

**Methods/Design:**

The proposed study will be a randomised controlled trial. After stratification for medical caregiver, athletes will be randomised to two study groups. One group will receive a standardized eight-week proprioceptive training program that has proven to be cost-effective to prevent recurrent ankle injuries, consisting of a balance board (machU/ MSG Europe BVBA), and a traditional instructional booklet. The other group will receive the same exercise program and balance board. However, for this group the instructional booklet is exchanged by the interactive ‘Strengthen your ankle’ App.

**Discussion:**

This trial is the first randomized controlled trial to study the implementation effectiveness of an App for proprioceptive balance board training program in comparison to a traditional printed instruction booklet, with the recurrence of ankle sprains among athletes as study outcome. Results of this study could possibly lead to changes in practical guidelines on the treatment of ankle sprains and in the use of mobile applications for injury prevention. Results will become available in 2014.

**Trial registration:**

The Netherlands National Trial Register NTR4027. The NTR is part of the WHO Primary Registries.

## Background

Ankle sprains are the most common sports and physical activity (PA) related injury [1-3]. It has been estimated that approximately 25% of all injuries across all sports are ankle injuries. Of all ankle injuries 85% involve the lateral ankle ligaments, i.e. acute lateral ankle sprains [3]. In the Netherlands, the most recent count of sports injuries showed that there is an estimated absolute number of 3.7 M acute sports injuries each year in a sporting population of 11 M athletes [4]. Of all annual sports injuries, approximately 530,000 are ankle sprains, of which almost 40 per cent requires (para) medical treatment [5]. Our research group has previously shown in a cost-effectiveness study [6] that, disregarding the requirement of medical treatment, the mean total (direct and indirect) cost of one ankle sprain is approximately €360. This would give a rough estimate of the annual sports-related ankle sprain costs in the Netherlands of €190,800,000. In addition, there is extensive evidence that there is an up to twofold-increased risk for ankle re-injury during the first year post-injury [6,7]. In fifty percent of all cases recurrences may result in disability and can lead to chronic pain or instability, requiring prolonged medical care [8]. As such, ankle sprains continue to pose a significant burden to the individual athlete, as well as to society as a whole.

Research has shown that both externally applied supports (i.e. taping or bracing of the ankle), as well as neuromuscular training programs are very successful in preventing recurrent ankle sprains, both from effectiveness, as a cost-effectiveness perspective [3,9-11]. While such measures have not been clearly linked to a primary preventive effect, the increased risk of recurrent injury can be reduced to the same level as previously uninjured athletes.

Therefore, in all current ruling treatment guidelines secondary preventive measures - preferably through continued neuromuscular training - are recommended after rehabilitation. These secondary preventive efforts regarding ankle sprains have been associated with high short-term returns on investment. The neuromuscular program that will be the centre of the proposed project has been linked to a €100 net return for each intervention package distributed [10].

However, despite ankle sprains being the single most common sports injury and despite an active approach by various Dutch organizations in implementing effective preventive measures and interventions, large-scale community uptake of preventive measures, and thus actual prevention of ankle sprains, is lagging well behind. This challenge can be derived from the Dutch injury rates registered by the Dutch Consumer Safety Institute VeiligheidNL [5], indicating that ankle sprain rates, treated at hospitals’ Emergency Departments, are consistent over the past years. In addition, the previously mentioned neuromuscular training program, that has been proven effective [8] and cost-beneficial [6], has been shown to have poor compliance [12]. In fact, the preventive effect in former studies was achieved in a subsample of compliant athletes, nevertheless showing significant population effects. Although analyses have been done from an intention-to-treat approach, this shows there is a lot to gain at an individual as well as a population level by increasing compliance to these simple and effective measures that are being advocated in various treatment guidelines.

In an attempt to bridge this implementation gap, VeiligheidNL looked into the possible role of new (social) media and has developed a freely available interactive ‘Strengthen your ankle’ App; available for iOS and Android) that contains - next to general advice on bracing and taping - the cost-effective neuromuscular program, as evaluated in a previous trial. This App provides the user withvideos and an interactive neuromuscular exercise schedule. It is a general belief that such interactive, online and mobile methods of information transfer are the way forward in prevention and implementation efforts. However, this has not yet been formally established for the uptake of injury preventive measures, and - although user reviews are positive - the ‘Strengthen your ankle’ App has not been evaluated against the well-studied ‘regular’ approach to advocate the neuromuscular program through written materials. Furthermore, if the ‘Strengthen your ankle’ App indeed does increase intervention uptake this will provide the necessary validation to further develop and enhance this promising role of new media in the implementation of preventive measures and interventions.

### Objectives

The objective of this randomised controlled trial is to evaluate the implementation value of the ‘Strengthen your ankle’ App as compared to the usual common practice of providing injured athletes with written materials.

Our hypothesis is that the use of the ‘Strengthen your ankle’ App will increase compliance to the prescribed neuromuscular training program and, consequently, will decrease ankle sprain recurrence incidence.

Specific research questions that will be answered are:

• What is the compliance to the prescribed 8-week exercise program via the App and via written material?

• Is there a difference in program compliance rates between the ‘Strengthen your ankle’ App and written materials?

• Is there a difference in ankle sprain recurrence incidence rates during a 12-month follow-up, between groups applying the ‘Strengthen your ankle’ App and written materials?

• Is there a difference in direct and indirect costs during a 12-month follow-up, between groups applying the ‘Strengthen your ankle’ App and written materials?

• Is there a difference in ankle sprain residual complaints (i.e. instability, feeling of giving way, pain, and continued sports participation) after a 12-month follow-up, between groups applying the ‘Strengthen your ankle’ App and written materials?

• What is the participants’ user experience of the ‘Strengthen your ankle’ App and the written materials?

## Methods

### Design

The proposed study will be a randomised controlled trial. The study design and flow of the athletes are shown in Figure 1. The study design, procedures and informed consent procedure were approved by the Medical Ethics Committee (no. 2013/248) of the VU University Medical Center Amsterdam (VUmc), the Netherlands. The trial is registered in the Netherlands Trial Registry (NTR4027).

**Figure 1 F1:**
[figure not shown]
Study design and flow of the athletes.

### Participants

Active participants (athletes), between 18 and 70 years of age, who have sustained an ankle sprain within the past two months, are eligible for inclusion. Responders are excluded if they have suffered from an injury different from a lateral ankle sprain in the same ankle (e.g. fracture of the ankle) in the previous year. Athletes should own a mobile phone with either Android of iOS. Athletes will be recruited through participating caregiving practices, websites from national sport federations, newsletters, an open invitation via the Internet and through the communication channels of participating sport associations.

### Study outline

#### ***Randomisation procedure***

After athletes have finished ankle sprain treatment by means of usual care, they will be randomised to one of the two study groups with stratification for initial treatment (i.e. medical or non-medical). Randomisation will take place at the end of treatment. This will minimise the risk of allocation bias. In addition, this will provide room to contact the medical care provider(s) involved in the athletes’ treatment. Medical care providers will be informed about the study in which the athlete partakes and will be asked to follow their usual treatment and/or rehabilitation program. Furthermore, they will be asked to encourage the athlete to take up their allocated intervention program after treatment and/or rehabilitation has ceased.

Athletes allocated to the ‘regular’ intervention group will receive a standardized eight-week proprioceptive training program, consisting of a balance board (machU/ MSG Europe BVBA), and an instructional booklet. This program has been shown to be effective in reducing recurrence injury risk in previous randomized controlled studies [9,10].

Athletes allocated to the ‘App’ group will also receive a balance board (machU/ MSG Europe BVBA), but the standardized eight-week proprioceptive training program will be provided through an interactive smartphone application, which is freely available for Android and iOS users. These two platforms are the most commonly used operating systems on smartphones (of all smartphones 79.3% runs on android, 13.2% on iOS) [13]. Thereby, selection bias is considered minimal. All athletes receive the same balance board. Both the instruction booklet and the ‘Strengthen your ankle’ App contain the same training program and six basic exercises (Figure 2).

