### Statistical analyses

All analyses will be carried out according to the intention-to-treat principle.

Compliance rates between groups will be compared by means of a multivariate linear regression analysis using compliance as a continuous dependent variable. Cox-regression analysis will be used to compare ankle recurrence risk between the intervention and the control group. Absence from sports will be compared between the two groups using a Mann–Whitney test, since absence from sports due to an injury is not normally distributed. For all analyses, variables will be checked for confounding and/or effect-modification and will be adjusted for accordingly.

Mean direct, mean indirect and total costs will be estimated and compared between the two groups, both for the costs per athlete in the injured population and for the costs per athlete in the total population. Because costs will not be normally distributed, 95% confidence intervals for the differences in mean costs will be obtained by bias-corrected and accelerated bootstrapping with 2000 replications. Differences in costs and differences in ankle sprain recurrences will be included in a cost-effectiveness ratio, which estimates the incremental costs to prevent one ankle sprain recurrence. Confidence intervals for the cost-effectiveness ratio will be calculated with bootstrapping, using the bias-corrected percentile method with 5000 replications. Uncertainty of this ratio will be evaluated by presenting a cost-effectiveness plane and sensitivity analyses will be performed to check the robustness of the results. An acceptability curve will also be presented.

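### The factor used to stratify randomisation is not pre-specified in any analysis; a data-driven confounding check that it will usually not trigger decides whether it is adjusted for

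*Protocol article*

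**What the plan says.** Under Randomisation procedure, the Methods say of athletes who have finished usual care that "they will be randomised to one of the two study groups with stratification for initial treatment (i.e. medical or non-medical". The Abstract (Methods/Design) words it differently: "After stratification for medical caregiver, athletes will be randomised to two study groups".

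The Statistical analyses section gives the primary analysis as follows: "Compliance rates between groups will be compared by means of a multivariate linear regression analysis using compliance as a continuous dependent variable". For recurrence, "Cox-regression analysis will be used to compare ankle recurrence risk between the intervention and the control group". Absence from sports is compared with a Mann–Whitney test, and costs by bootstrap. The stratification factor is named in none of these. The only covariate rule is general: "For all analyses, variables will be checked for confounding and/or effect-modification and will be adjusted for accordingly".

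Two statements bear on whether the factor could predict outcome. Of the medical care providers, the Randomisation procedure says that "they will be asked to encourage the athlete to take up their allocated intervention program after treatment and/or rehabilitation has ceased". The section on usual care says that 60 per cent of ankle sprains, mostly minor ones, are self-treated.

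**The concern.** A factor chosen for stratification is normally kept in the analysis, because stratification makes the treatment estimate more precise than a model without the factor can recognise. The between-stratum variance stays in the residual, and the reported standard error exceeds the true sampling variability.

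The rule in this article works against that. A confounding check looks for a factor that differs between arms and shifts the treatment estimate when it is added. Stratified randomisation prevents that imbalance, so the factor will usually not be flagged, however strongly it predicts outcome. The decision to adjust is also taken after the data are seen, when it could be fixed now.

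At stake are some precision in the compliance analysis and one avoidable data-dependent choice in the primary model. The differing description in the Abstract matters less, but a pre-specified term needs one definition.

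**Working it through.** **The plan's own figure.** The sample size section takes 25% against 50% full compliance, alpha 0.05, and a beta of 0.90 read as 90% power. With a two-sided test and mean rate 0.375:

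n per arm = 2 × 0.375 × 0.625 × (1.96 + 1.2816)² / 0.25² = 78.8, so 79 per arm and 158 in total.

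This reproduces the stated 158. The figure does not depend on the stratification factor.

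**Inputs for the consequence.** The document gives no figure for R2, the share of outcome variance that initial treatment explains. A range is therefore assumed. The effect size is set so that a design with R2 = 0 has 90% power.

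**Formulas** (large-sample, arms balanced within strata):

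- Standard error without the factor relative to with it: 1/√(1 − R2)
- True type I error without the factor: 2 × [1 − Φ(1.96/√(1 − R2))]
- Power without the factor: Φ(1.2816/√(1 − R2))
- Power with the factor: Φ(3.2416/√(1 − R2) − 1.96)

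| Assumed R2 | SE ratio | Type I error, factor omitted | Power, omitted | Power, included |
|---|---|---|---|---|
| 0 | 1.000 | 5.0% | 90.0% | 90.0% |
| 0.01 | 1.005 | 4.9% | 90.1% | 90.3% |
| 0.05 | 1.026 | 4.4% | 90.6% | 91.4% |
| 0.10 | 1.054 | 3.9% | 91.2% | 92.7% |
| 0.20 | 1.118 | 2.8% | 92.4% | 95.2% |
| 0.30 | 1.195 | 1.9% | 93.7% | 97.2% |

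For R2 = 0.10, √0.90 = 0.9487. Then 1/0.9487 = 1.054, and 1.96/0.9487 = 2.066 gives 3.9%. For power, 1.2816/0.9487 = 1.351 gives 91.2%, and 3.2416/0.9487 − 1.96 = 1.457 gives 92.7%.

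**Simulation check.** The set-up was 158 athletes, permuted blocks of four within two strata (40% medical, assumed), a standardised continuous outcome and 3,000 replications per scenario. At R2 = 0.10 the type I error was 0.037 without the factor and 0.046 with it; power was 0.914 and 0.930. At R2 = 0.20 the figures were 0.026 and 0.046, and 0.923 and 0.951. Bias was about zero in both models throughout.

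**Which R2 is plausible?** As an illustration only, suppose 40% of athletes are medically treated, with 40% full compliance among them and 15% among the self-treated. The mean is 0.4 × 0.40 + 0.6 × 0.15 = 0.25, the planned control rate. Then R2 = 0.4 × 0.6 × 0.25² / (0.25 × 0.75) = 0.08. With the same mix and mean, R2 = 0.20 needs a difference of √(0.20 × 0.1875/0.24) = 0.395, or about 49% against 9%, which nothing in the article supports. The rows up to 0.10 are therefore the relevant ones. The illustration uses binary full compliance, whereas the planned model uses continuous compliance, so it is only a guide.

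**The case against.** The strongest reply is that an article need not list covariates, and that adjustment is not excluded: the rule covers all analyses, treatment of the current sprain is recorded at baseline, and effect modification is a second route into the model that balance between arms does not close. This stands in part. It would be wrong to say that the factor is left unadjusted; it is not pre-specified. But the article does more than stay silent. It fixes a covariate rule, and that rule tends to pass over the factor that the trial randomises by.

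A reader might infer that the standard errors are too wide and that initial treatment is tied to compliance. The document supports neither as fact. It reports no such association. The encouragement request and the milder injuries of self-treated athletes make a link plausible, no more, and the 60 per cent describes ankle sprains in general, not this trial's sample.

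A reader might also infer that the trial loses needed power or risks a false positive. The error is conservative, the linear estimate is unbiased, and power without the factor stays at or above the planned 90% in every row of the table. What is lost is extra efficiency. An unadjusted Cox hazard ratio may lie closer to 1 than an adjusted one, but that is a difference between marginal and conditional effects, and no size can be given from this document.

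Finally, the two descriptions of the factor might be taken as real doubt about the design. The Methods give explicit levels, and the recruitment section treats randomisation at caregiver level as a complication, so the Abstract most likely uses a shorthand. This is mainly a wording fix.

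**Conclusion.** The point holds in limited form. The stratification factor is pre-specified in no analysis, and the stated rule will usually not bring it in. If initial treatment predicts compliance and is omitted, the linear-model standard error is about 0.5% too wide at R2 = 0.01, 3% at 0.05 and 5% at 0.10. At 0.10 the type I error is about 3.9%, and power about 91% against 93% with the factor included. If it does not predict compliance, nothing is lost. These figures rest on an assumed R2, balanced arms within strata, and an effect that gives 90% power at R2 = 0. The consequence is small and in the safe direction; the case for change is that it is free and removes a data-dependent choice from the primary analysis.

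**What to change.** - In Statistical analyses, state that the stratification factor is a pre-specified term in the primary compliance regression and a covariate or stratum in the Cox model, whatever the check for confounding or effect modification shows.
- Make the Abstract agree with the Methods on what the factor is: initial treatment, medical or non-medical.
- Optional: a rank test stratified by the same factor (van Elteren) for absence from sports, and bootstrap resampling within strata for costs.

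The cost is a few sentences and, if the optional steps are taken, slightly different code. No new data are needed, since the baseline questionnaire already records treatment of the current sprain. The sample size does not change.

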**Figure 2 F2:**
[figure not shown]
Basic exercises of the ‘Strengthen your ankle’ proprioceptive training program.

### Baseline measurement

The online baseline questionnaire gathers information of each athlete on demographic variables, physical characteristics, sports & injury history, use of preventive measures, knowledge on injury prevention, severity of the current ankle sprain and subsequent treatment and/or rehabilitation.

### Follow-up measurement

After the 8-week training program, athletes will receive an online follow-up questionnaire to measure residual complaints of the initial ankle sprain and attitude towards the prescribed exercises. Both pain and feeling of giving way will be scored on five-point Likert scale for a series of questions.

Recurrent injury incidence and cost of injury outcomes will be measured once a month for a total period of 12 months. The follow-up measurements will gather information for each athlete on ankle sprains sustained during the preceding month, including details and mechanisms of this sprain and absence from sports due to the ankle sprain recurrence as a measure of recurrence severity. Finally, these online follow-up questionnaires will measure residual complaints of the initial ankle sprain. Both pain and feeling of giving way will be scored on five-point Likert scale for a series of questions, e.g. do you feel pain when being active, do you feel pain when getting out of bed in the morning, do you feel your ankle giving way when walking across the street, etc. At the last follow-up measurement (12 months) residual complaints of the initial ankle sprain will be measured again in all athletes.

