### Compliance

Compliance (primary outcome) measurements will commence after randomisation (i.e. after treatment and at the start of the allocated intervention), and will take place weekly for the duration of the program (8 weeks). These measurements will gather information for each athlete on the number and sets of executed exercises. In addition, online questions will be asked regarding the clarity of the instructions provided, difficulty of the exercises and recurrence of an ankle sprain.

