### Cost diary

In order to evaluate the cost-effectiveness of the allocated interventions, athletes who sustain an ankle sprain recurrence will be contacted by phone to obtain information on costs associated with treatment. Based on this information direct and indirect costs resulting from the sustained ankle sprain recurrence will be calculated for use in an economic evaluation. The economic evaluation will be performed from a societal perspective.

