### Sample size

Sample size calculations are based upon the primary outcome measure compliance, and are based upon previously established compliance rates to the same program when advocated through written materials [12]. Full compliance rates in the written materials’ group are expected to be around 25%. A doubling of this rate to at least 50% is considered to be clinically relevant. Based upon a beta of 0.90 and an alpha of 0.05 a total of 158 athletes is required divided across both study groups. In our experience from previous comparable studies the dropout rate during a 12 months follow-up is about 20%. This would mean that a sample of 190 athletes is needed per group.

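### Monthly questionnaires ask about sprains in the preceding month with no described look-back, so after week 8 a sprain in a skipped month may go unrecorded

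*Protocol article*

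**What the plan says.** All references are to the protocol article.

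- **Follow-up measurement** sets the schedule, "Recurrent injury incidence and cost of injury outcomes will be measured once a month for a total period of 12 months", and the recall window, "The follow-up measurements will gather information for each athlete on ankle sprains sustained during the preceding month". Sports absence after a recurrence is collected in the same questionnaires.
- **Follow-up measurement**, on the final contact: "At the last follow-up measurement (12 months) residual complaints of the initial ankle sprain will be measured again in all athletes". This is the only item named for repetition at month 12. A recall of sprains over the whole year is not mentioned.
- **Compliance** gives a second source. The weekly measurements "will take place weekly for the duration of the program (8 weeks"), and their online questions include "difficulty of the exercises and recurrence of an ankle sprain".
- **Cost diary**: "athletes who sustain an ankle sprain recurrence will be contacted by phone to obtain information on costs associated with treatment". The call follows a recurrence that is already known.
- **Statistical analyses**: "Cox-regression analysis will be used to compare ankle recurrence risk between the intervention and the control group". The recurrence difference also enters the cost-effectiveness ratio.
- **Sample size** expects that "the dropout rate during a 12 months follow-up is about 20" per cent. No response rate per questionnaire is given anywhere.

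**The concern.** A fixed one-month window works as long as every questionnaire is answered. Take an athlete who skips month 4 and answers month 5. Followed as described, the month-5 questionnaire asks about month 5, and nothing described afterwards asks about month 4. A sprain in month 4 then leaves no trace. Its sports absence is missed because it belongs to the same questionnaire. Its treatment costs are missed because the phone call depends on knowing of the recurrence.

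Compliance is the primary outcome and the sample size rests on it. Recurrence is nevertheless the second half of the hypothesis under Objectives, the study outcome named in the abstract's discussion, and the effect term of the cost-effectiveness ratio. One missed answer can therefore touch recurrence, absence and costs together. This is a matter of data collection: an analysis plan can decide how to treat an uncovered month, but it cannot restore a sprain that nobody asked about.

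**Working it through.** The plan states no figure on this point, so there is none to reproduce. The check first sets the data sources side by side and then sizes the gap under stated assumptions.

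**Step 1. Which source covers which period?**

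| Source | Period | Could it catch a sprain in a skipped month? |
|---|---|---|
| Weekly compliance questions | Weeks 1–8 | Yes, within those weeks |
| Monthly questionnaire | 12 months, preceding month each time | Not as described |
| Month-12 measurement | End of follow-up | Repeats residual complaints; no year-long recall of sprains described |
| Cost phone call | After a known recurrence | Not described as a way of finding one |

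Taking 8 weeks as about 2 months, some 10 of the 12 months depend on the monthly question alone.

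**Step 2. Inputs for size, all assumptions.** Share of monthly questionnaires skipped, m: 10–20% (wider range 5–30%). Skipping is unrelated to injury. Recurrences are spread evenly over the year. A sprain in a skipped month is lost. For the athlete-level check, 12-month risk is 20–40%; the article gives no absolute risk.

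**Step 3. Equal skipping, share of recurrences lost.**

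- Monthly questions as the only source: loss = m, so 10% to 20%.
- Weekly questions catching everything in months 1–2: loss = m × 10/12, so 0.10 × 10/12 = 8.3% to 0.20 × 10/12 = 16.7%.

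The combined range is roughly 8–20%. Both arms lose the same fraction, so the ratio is about unchanged: 0.90/0.90 = 0.80/0.80 = 1. The standard error of a log hazard ratio varies roughly as 1/√(events), so it rises by a factor of 1/√0.917 = 1.04 to 1/√0.80 = 1.12.

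**Step 4. Athlete-level check.** With 12-month risk R, the monthly risk is p = 1 − (1 − R)^(1/12).

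- Observed risk, monthly questions only: 1 − (1 − p(1 − m))^12.
- Observed risk, months 1–2 fully caught: 1 − (1 − p)^2 × (1 − p(1 − m))^10.

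For R = 30% and m = 10%, p = 0.0293 and the observed risks are 27.4% and 27.9%. Over R = 20–40% and m = 5–30%, the share of athletes with a recurrence who are missed runs from 4% to 28% (monthly only) or 3% to 23% (with weekly questions).

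**Step 5. Unequal skipping, true ratio 1.** This step adds one assumption: skipped months count as event-free time at risk. The apparent App-to-booklet ratio is then (1 − loss in App) / (1 − loss in booklet).

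| Skipped, App vs booklet | All 12 months exposed | 10 of 12 months exposed |
|---|---|---|
| 10% vs 20% | 0.90/0.80 = 1.13 | 0.917/0.833 = 1.10 |
| 20% vs 10% | 0.80/0.90 = 0.89 | 0.833/0.917 = 0.91 |

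The two rows mirror each other, and nothing in the article says which applies.

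**The case against.** The strongest reply is that one sentence in a condensed article is a summary, not the questionnaire. For an instrument sent every month, the preceding month is natural shorthand. The full protocol may hold the item wording, reminders or late completion, and a short fixed window is a recognised way to limit recall error. This stands against any claim of certainty, and for that reason the point says that a sprain may go unrecorded. It does not remove the point, because the recall window is a stated rule and no described contact after week 8 reaches back over a gap.

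Three stronger readings are tempting, and the document does not support them.

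- *The monthly questionnaires are the only source of recurrences.* The weekly measurements under Compliance also ask about them.
- *The athlete stays in the Cox model as event-free during the skipped month.* Statistical analyses gives no rule for missed months. That rule commonly sits in the analysis plan, which is not shown, so its absence is no finding.
- *The comparison is biased against the App because the booklet arm will engage less.* The hypothesis concerns exercise compliance, not questionnaire response. Likewise, the 20% dropout figure shows only that incomplete follow-up is expected; it does not measure intermittent skipping.

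It is also fair to say that the size rests wholly on assumed skip rates and that recurrence is not the primary outcome.

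**Conclusion.** The point holds as a gap in ascertainment. As described, a sprain in a skipped month after week 8 can be lost, with its absence and costs, and no analysis can bring it back. With an assumed 10–20% of monthly questionnaires skipped equally, about 8–20% of recurrences could go, at a cost in precision and with little change in the hazard ratio.

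Bias needs more: skipping that differs between arms, or that is related to injury (not quantified here). The 1.10–1.13 example additionally depends on skipped months being counted as event-free. If uncovered months were instead left out of the time at risk, and skipping were unrelated to injury, the hazard ratio would be largely protected, but the events would still be missing. The direction of any bias cannot be settled from the document. How missed months are censored is for the analysis plan and is not part of this finding.

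**What to change.** Word the recurrence item in each monthly questionnaire as *since your last completed questionnaire on [date]*, with the date filled in for each athlete, and ask the date of every sprain reported. A sprain from a skipped month can then be placed in the right month, and its absence and costs can be followed up through the existing questions and phone call.

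The cost is a small change to one online question, made before the questionnaires go out. The downside is somewhat longer recall for athletes who skipped a month; those who answer every month keep essentially the same window. The change helps only athletes who return after a gap. It does nothing for those who stop responding altogether.
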